### Ethical considerations and informed consent

Ethics approval was obtained from the National Research Ethics Service (London Brent Committee; REC reference: 11/LO/1726). The study will be conducted according to the Declaration of Helsinki (sixth revision) and Good Clinical Practice guidelines. The investigator or co-investigator will explain the nature, purpose, and risks of the study to the participant. The participant will receive the information sheet in advance of the study sessions. There will be no time restriction on how long participants take to respond, with the exception that participants who respond after all study places have been filled will not be offered a place on the study. Therefore, participants will be given sufficient time to read the information and consider any implications, and to raise any questions with the investigators prior to making a decision to participate. Participants will be informed that they are free to withdraw at any time.

### Sample size determination

As our primary objective is to investigate the effects of CBM training on neural response to smoking-related cues, the sample size determination was based on this outcome. However, the effects of cognitive bias on neural responses to smoking cues have not been evaluated in previous research. To estimate the required sample size we used data from our previous study [19] that indicated a likely increase in the cognitive bias index of 30 ms in the attend group, and a decrease of 30 ms in the avoid group. We assume that the change in the control condition will be intermediate (0 ms). We will therefore achieve greater than 80% power to detect a linear effect across the three CBM groups on change in cognitive bias index with a total sample size of n = 30, at an alpha level of 0.05. Using data from a study that compared craving in response to smoking cues in groups who had received treatment of varenicline (mean = 11.2, standard deviation = 4.7) versus placebo (mean = 14.6, standard deviation = 4.7), we estimate a total sample size of 64 is required to achieve 80% power at an alpha level of 0.05. As we expect some attrition, we will use a more conservative estimate of n = 72.

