Each participant’s fMRI data will then be entered into a first-level voxel-by-voxel analysis using the general linear model. Each cue block (smoke or control) will be modelled as a boxcar function convolved with a canonical hemodynamic response function that begins at the onset of the first cue in the block and ends at the end of the block (60-second duration). A high-pass filter will be applied to remove slow signal drift. A smoking-related cue greater than control cue contrast image will then be created and inputted into a random effects analysis. A two (varenicline and placebo) × three (attend, avoid, and control) mixed-model analysis of variance (ANOVA)will be used to examine smoking cue reactivity (smoking greater than control) between each group. Voxel-wise analysis will be conducted within an Region of Interest (ROI) mask. The mask will be created from anatomical regions identified in a meta-analysis of cue reactivity [31]: nucleus accumbens, caudate, putamen, temporal gyrus, anterior cingulate gyrus, amygdala, insula, posterior cingulate cortex, inferior frontal gyrus, and angular gyrus. Each bilateral region will be selected using the WFU PickAtlas tool [32] and combined to create the mask. Resulting activations will be considered significant at an alpha level of 0.001 (uncorrected) with a minimum cluster extent threshold of 20 contiguous voxels. *Post hoc* analyses of parameter estimates will be used to evaluate the nature of significant effects. Smoking cue greater than control cue contrast images for each participant will also be input into random effect regression analyses examining relations between post-training cognitive bias scores and neural cue reactivity.

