#### Cognitive bias analyses

Cognitive bias scores will be calculated from reaction time (RT) data from the visual probe task, by subtracting RTs to probes that replace smoking-related pictures from RTs to probes that replace neutral pictures, so that positive scores represent a bias towards smoking cues and negative scores represent a bias towards neutral cues. These bias scores will be used to examine cognitive training effects in a two (pre- and post-CBM) × two (varenicline and placebo) × three (attend, avoid, and control) mixed-model ANOVA.

A two (smoking cue and neutral cue) × two (pre- and post-CBM) × two (varenicline and placebo) × three (attend, avoid, and control) mixed-model ANOVA will also be conducted on the modified Stroop task RT and error data. Participants will be excluded if their mean RT or error score is three standard deviations (or more) below or above the sample mean.

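### The sample size claims power for a linear attend–control–avoid trend, but the planned ANOVAs test a 2-df CBM effect and give hypotheses 1 and 2 no test of their own

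*Protocol article*

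**What the plan says.** **Powered test.** Under Sample size determination, the article takes from an earlier study "a likely increase in the cognitive bias index of 30 ms in the attend group, and a decrease of 30 ms in the avoid group". For the third arm it adds: "We assume that the change in the control condition will be intermediate (0 ms)". From these values it concludes: "We will therefore achieve greater than 80% power to detect a linear effect across the three CBM groups on change in cognitive bias index". The claim is made for 30 participants in all and alpha 0.05. It gives no SD and does not say whether the test is one- or two-sided. The final 72 comes from a separate varenicline calculation (64, raised for attrition).

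**Planned tests.**
- Dot-probe (Cognitive bias analyses): "These bias scores will be used to examine cognitive training effects in a two (pre- and post-CBM)" × two (drug) × three (CBM) mixed-model ANOVA. No follow-up is stated.
- Neural response (fMRI analysis): "A two (varenicline and placebo) × three (attend, avoid, and control) mixed-model analysis of variance (ANOVA)will be used to examine smoking cue reactivity", judged voxel-wise at 0.001 uncorrected with at least 20 contiguous voxels. Post hoc "analyses of parameter estimates will be used to evaluate the nature of significant effects".

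**Hypotheses.** Under Study objectives and hypotheses, hypothesis 1 predicts that attend training raises bias and neural response. Hypothesis 2 predicts that avoid training lowers both. They are separate and directional.

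**The concern.** The test that carries the power statement is absent from the statistical plan. Assumed changes of +30, 0 and −30 ms tested for a linear effect form a single ordered contrast. In the named ANOVAs the CBM effect (time × CBM for bias, CBM for the neural contrast) spreads the same signal over two degrees of freedom, one of them for a departure from linearity that no hypothesis predicts.

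The second issue is interpretation. Neither a significant omnibus effect nor a linear trend alone shows whether attend moved, avoid moved, or both did. Hypotheses 1 and 2 ask exactly that. The control arm could separate them, but no planned contrast uses it. If the choice among trend, omnibus and pairwise tests is left until results are seen, the main CBM conclusion depends on that choice.

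**Working it through.** **Inputs from the article:** mean changes +30, 0, −30 ms; total 30 (10 per group) for the power claim; total 72 (24 per CBM group) enrolled; alpha 0.05 for bias and 0.001 voxel-wise for fMRI.

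**Assumed, because not given:** the SD of change, equal across groups; a two-sided test unless stated otherwise; the neural effect sizes.

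**1. The article's own figure.** It cannot be reproduced without an SD, so I solved for the SD that makes it just true.
- Noncentrality of the linear contrast: δ = 60 / (SD × √(2/g)), where g is the number per group and df = N − 3.
- With g = 10 and df = 27, the two-sided 0.05 critical value is 2.052. Power of 80% needs δ = 2.906.
- SD = 60 / (2.906 × √0.2) = 60 / (2.906 × 0.4472) ≈ 46.2 ms.

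Since the article claims more than 80%, 46 ms is a ceiling if the test was two-sided. If it was one-sided, the ceiling is about 53 ms.

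**2. The planned 2-df test with the same inputs.**
- λ = g × (30² + 0² + 30²) / SD².
- At 30 participants: 10 × 1800 / 46.16² = 8.45. With F(2, 27) and critical value 3.354, power is 69%. Reaching 80% needs 39 participants.
- At 72 participants: λ = 24 × 1800 / 46.16² = 20.27, power 98%. The linear contrast (δ = 4.50) has 99%.

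Bias index at 72, by assumed SD:

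| SD (ms) | Linear | Omnibus |
|---|---|---|
| 40 | 99.9% | 99.7% |
| 46 | 99% | 98% |
| 60 | 93% | 87% |
| 80 | 73% | 62% |

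SDs of 60 and 80 ms exceed the ceiling in step 1, so those rows apply only if the article's power claim is wrong.

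**3. Each trained arm against control.** The difference is 30 ms with 24 per group; two-sample t, df = 46, two-sided 0.05; δ = 30 / (SD × √(2/24)).

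| SD (ms) | Power |
|---|---|
| 46 | 60% |
| 40 | 72% |
| 35 | 83% |
| 30 | 92% |

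Pooling the error over all three groups changes these by at most about one point. At 46 ms, testing each comparison at 0.025 gives 49%, and 80% power at 0.05 would need about 114 in total. If the trend test was one-sided (SD 53 ms), the omnibus test has 57% at 30 and 94% at 72, and each arm against control has 50% at 72.

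**4. Neural outcome, one voxel at 0.001, 72 participants, df = 66.** Let d be the standardised attend–avoid difference with control midway. Then δ = d / √(2/24) and λ = 24 × d²/2. Both tests are non-directional.

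| d (assumed) | δ | λ | Linear, two-sided | Omnibus F |
|---|---|---|---|---|
| 1.3 | 4.50 | 20.28 | 85% | 75% |
| 1.0 | 3.46 | 12.00 | 51% | 39% |
| 0.8 | 2.77 | 7.68 | 26% | 18% |

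The value 1.3 is the bias-index effect carried over (60 / 46.2). The other two are illustrations. The cluster-extent rule is ignored.

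**The case against.** **Power.** A reader might infer from 80% against 69% that the trial is underpowered for its CBM effect on bias. The documents do not support that: the 69% belongs to 30 participants and the trial enrols 72. At the implied SD the loss is then about one point, and at 64 completers it is still only 98.7% against 96.8%. This objection stands.

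**The SD.** The 46 ms is a bound, not an estimate. On a two-sided reading, 60% for each arm against control is therefore a floor, and the true figure could be above 90%. This also stands.

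**Neural figures.** The article says these effects have not been evaluated before, so no effect size can be taken from it. A one-sided contrast set against the F test would show a larger gap, but part of it would come from sidedness rather than from the degree of freedom. The like-for-like comparison is the one shown above.

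**Comparator and follow-up.** Hypotheses 1 and 2 do not name control. For bias they can be read as pre-to-post change within an arm. Control is the natural comparator for the neural outcome, which is scanned once, but that is a reading and not the protocol's wording. Nor does the plan make dot-probe follow-up conditional on a significant F: the post hoc sentence belongs to the fMRI section only.

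**Condensed article.** Planned contrasts are often left to a fuller analysis plan and can be estimated from the named models. That excuses missing detail. It does not remove the mismatch, because the article itself states both the powered test and the planned tests, and they differ.

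**Conclusion.** The point holds as an inconsistency with a modest power cost and a larger cost in interpretation. The one-df linear test behind the power claim is not in the statistical plan, and no planned contrast tests hypothesis 1 or 2 separately.

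For the bias index at 72, the omnibus test costs about one point of power if the SD is at the 46 ms ceiling. Judged against control, hypotheses 1 and 2 have about 60% power at that SD and 92% at 30 ms, and the trend calculation does not show this. For the neural response, which the article calls the primary objective, the omnibus test gives up about 10, 12 or 13, and 8 points at assumed d of 1.3, 1.0 and 0.8.

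These sizes rest on a back-solved SD, equal variances, a two-sided trend test and illustrative neural effects. The mismatch itself rests on none of them.

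**What to change.** Within the models already named:

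1. Prespecify the linear contrast (attend +1, control 0, avoid −1) as the primary CBM test, both for dot-probe change and for the smoking-greater-than-control images.
2. Prespecify attend-versus-control and avoid-versus-control, with a multiplicity rule, as the tests of hypotheses 1 and 2, and state that control is the comparator.
3. Keep the omnibus F and the drug × CBM interaction as secondary.
4. State the SD and sidedness behind the figure of 30, and the power of the two pairwise tests at 24 per group.

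The cost is wording: same data, same models, no extra participants. With 55 of 72 enrolled as of March 2014 and collection projected to end in June 2014, this could still be fixed before the data were complete. There are two downsides. A non-monotone pattern would show only in the secondary omnibus test, and the pairwise power, once stated, may look less favourable than the trend figure.

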### Study objectives and hypotheses

The primary objective is to investigate the neural effects of CBM in response to smoking-related cues in current daily smokers. A secondary objective is to examine the effects of varenicline treatment on neural responses to smoking cues. We will also explore whether there is any pattern in the data to suggest that the effects of CBM are modified by concurrent treatment with varenicline. The CBM methods we will use are delivered via computer, and can therefore in principle be delivered remotely and repeatedly at low cost, for example via the internet or smartphones, as an adjunctive treatment to varenicline pharmacotherapy. To investigate whether CBM and varenicline effects generalize to other measures of cognitive bias, participants will also complete a modified pictorial Stroop task before and after CBM and varenicline.

We hypothesize that: 1) CBM designed to induce cognitive bias towards smoking-relates cues will lead to an increase in cognitive bias and neural response to smoking-related cues in brain regions previously implicated in cue reactivity in cigarette smokers; 2) CBM designed to induce cognitive bias away from smoking-relates cues will lead to a decrease in cognitive bias and neural response to smoking-related cues in brain regions previously implicated in cue reactivity in cigarette smokers; and 3) varenicline treatment will lead to a reduction in the neural response to smoking-related cues.

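### The sample size is said to rest on the neural outcome, but both calculations use other outcomes at alpha 0.05, so the stated 80% does not carry over to the neural varenicline test at 0.001

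*Protocol article*

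**What the plan says.** All references are to the protocol article.

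- **Study objectives and hypotheses** makes the neural effect of CBM the primary objective and the neural effect of varenicline a secondary one. The third hypothesis is that "varenicline treatment will lead to a reduction in the neural response to smoking-related cues".
- **Sample size determination** names the effect of CBM on neural response as the primary objective and says "the sample size determination was based on this outcome". It then concedes that "the effects of cognitive bias on neural responses to smoking cues have not been evaluated in previous research" and turns to two other outcomes.
  - For CBM it claims more than 80% power at alpha 0.05 for a "linear effect across the three CBM groups on change in cognitive bias index with a total sample size of n = 30". The assumed changes are +30, 0 and -30 ms, and no SD is given.
  - For the drug it proceeds thus: "Using data from a study that compared craving in response to smoking cues", with means of 11.2 (varenicline) and 14.6 (placebo) and an SD of 4.7 in both groups. From these, "we estimate a total sample size of 64 is required to achieve 80% power at an alpha level of 0.05". Expected attrition takes the target to 72.
- **functional Magnetic Resonance Imaging analysis** sets a different criterion for the neural outcome: "Resulting activations will be considered significant at an alpha level of 0.001 (uncorrected", with at least 20 contiguous voxels required as well. The test is a 2 × 3 ANOVA run voxel by voxel within a mask of anatomical regions.

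**The concern.** The sample size paragraph names one outcome and calculates for two others. The calculation that sets the number recruited also belongs to the secondary drug question, not to the primary CBM question with which the paragraph opens.

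The significance level changes too. The sizing uses 0.05 and the neural decision rule uses 0.001, which is 0.05/0.001 = 50 times stricter, with a cluster extent requirement on top. Even if the craving effect is accepted as a stand-in for the neural effect, the 80% is computed at a level that the neural analysis will not use.

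The practical risk lies in how a null varenicline result on the neural outcome is read. The Background describes earlier imaging samples for varenicline as small and in need of replication. A reader who takes the sizing to be for the neural outcome could treat a null here as a failed replication in an adequately powered study. The document does not support that.

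**Working it through.** **Inputs**

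- Drug effect on craving, from Sample size determination: difference 14.6 - 11.2 = 3.4, SD 4.7, so d = 3.4/4.7 = 0.723.
- Allocation 1:1, from Randomization (two batches, each with 18 varenicline and 18 placebo bottles).
- Sizing alpha 0.05; neural threshold 0.001. Sidedness is not stated.

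**Formula.** Two-sample t-test with N/2 per arm: noncentrality λ = d × √(N/4); power = P(|T| > t-critical) for T noncentral t with N - 2 df.

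**Step 1. Reproduce the plan's figure (alpha 0.05, two-sided)**

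| N | λ | t-critical | Power |
|---|---|---|---|
| 62 | 2.848 | 2.000 | 80.0% |
| 64 | 2.894 | 1.999 | 81.3% |
| 72 | 3.069 | 1.994 | 85.7% |

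The smallest N is 62, within 2 of the stated 64. A one-sided test needs only 50, so the two-sided t-test is taken as the plan's method. The arithmetic behind 64 is sound.

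**Step 2. Change only the alpha, to 0.001**

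| N | λ | t-critical, two-sided | Power, two-sided | Power, one-sided |
|---|---|---|---|---|
| 64 | 2.894 | 3.454 | 30.1% | 37.9% |
| 72 | 3.069 | 3.435 | 36.7% | 45.0% |

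With the error df of the 2 × 3 ANOVA (N - 6), the two-sided figures are 29.8% and 36.4%.

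**Step 3. What 0.001 would require**

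- N for 80% power at d = 0.723, two-sided: 136 with N - 2 df (80.02%). With N - 6 df, 136 gives 79.9%, so 138 is needed.
- Drug difference detectable with 80% power, two-sided: 1.08 SD at N = 64 and about 1.01 to 1.02 SD at N = 72, against the 0.72 SD used for sizing.

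**Step 4. Does this extend to CBM?** No SD is given for change in the bias index, so power at 0.001 cannot be derived from the document. As an assumption, take the largest SD that gives exactly 80% at n = 30 and alpha 0.05. The contrast is attend minus avoid, 60 ms, with N/3 per group, so λ = 60/(SD × √(2/10)) on 27 df. This gives SD = 46.2 ms. With that SD at 0.001 two-sided, power is 78% at N = 64 and 85% at N = 72. This is still a reaction-time measure, not a neural one.

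**What Step 2 does and does not measure.** It describes one voxel, and it assumes that an effect on a craving score has the same standardised size on the smoking-minus-control image contrast. The 20-voxel rule makes a declared finding harder. A search over a mask with several truly active sites makes at least one finding more likely. If sites were independent and the extent rule is ignored, the chance of at least one detection is 1 - (1 - p)^k. With p = 0.301 to 0.367 this is 66% to 75% for k = 3 and 83% to 90% for k = 5. Spatial correlation and the extent rule would pull these down.

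**The case against.** The strongest reply is that the paragraph is open about what it does. Straight after naming the neural outcome it says that no earlier data exist, and it then names the outcomes it uses instead. It never states 80% power for a neural measure. Borrowing an effect size from a related outcome is ordinary practice when none exists for the outcome of interest. This stands, and it means the fault is in the claimed basis and the unmatched alpha, not in the use of surrogates. Naming a surrogate does not tell the reader that the neural test will be run at another significance level.

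A second reply is that 30% to 37% is not the power of the planned analysis. That also stands. Nothing in the document links the craving scale to an imaging contrast, and a single voxel is not the mask-wide search. The true figure could lie on either side.

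A third is that the drug effect on neural response is secondary, and that change in dot-probe bias is itself a named primary outcome which the n = 30 calculation addresses directly. Both are correct and limit the reach of the point.

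A reader might infer that the trial has about one-third power for its primary objective, or that 64 was miscalculated. The document supports neither: no SD is given for CBM, the illustration in Step 4 gives 78% to 85%, and 64 reproduces.

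**Conclusion.** The point holds in a limited form. The statement that sizing was based on the neural outcome is not borne out by either calculation. The 80% attached to n = 64 belongs to craving at alpha 0.05, and it does not transfer to the neural varenicline test at 0.001 with a 20-voxel extent.

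The size of the gap can only be illustrated. Two-sided, at one voxel, with the craving effect carried over unchanged, power falls from 81% to 30% (N = 64) or from 86% to 37% (N = 72). The power of the full mask-wide analysis cannot be fixed from the document, and no shortfall for CBM should be claimed. Whether 0.001 uncorrected controls false positives is a separate question that is not addressed here.

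**What to change.** Keep n = 72 and revise the text of Sample size determination:

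1. Replace the sentence on the basis of the sizing. Say that it rests on change in the dot-probe bias index (n = 30) and on cue-elicited craving for varenicline versus placebo (n = 64, raised to 72), both at alpha 0.05, and that no power is claimed for the neural outcome at 0.001.
2. If a neural figure is wanted, give either the single-voxel power (about 30% at N = 64, 37% at N = 72) or the detectable drug difference (about 1.0 to 1.1 SD). State the assumptions beside it: craving effect size carried over where power is quoted, two-sided test, one voxel, extent rule and multi-site search not included.
3. State that a non-significant varenicline effect on neural response will not be read as absence of an effect.

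The cost is wording only, with no extra participants or data. Enrolment, at 55 in March 2014 according to Trial status, is unaffected. The downside is that the implied power for the neural outcome looks less favourable.

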### Randomization

Participants will be randomly assigned to drug and CBM groups, but equal numbers of participants per group will be maintained. The drugs will be prepared by University Hospitals Bristol Pharmacy who will produce two batches of 36 bottles (one for males and one for females) that comprise 18 bottles of varenicline and 18 bottles of placebo. Each bottle will be given a numeric identifier that enables study staff involved in data collection to be fully blinded to drug condition.

In advance of the study, an experimental collaborator (who will have no direct contact with the study participants) will prepare a numeric code using random number assignment software to further randomize participants to CBM groups. Randomization will be stratified so that equal numbers of male and female participants will be allocated to each experimental cell.

